#### Patient-Reported Outcome Measures (PROM)

Patient-reported performance status (PRPS) will be assessed using the ECOG performance status [56]. To measure symptom burden, the M.D. Anderson Symptom Inventory (MDASI) version 1 will be used [57]. MDASI is a multi-symptom PROM assessing the severity of symptoms and their interference with daily living [57]. To assess QoL, the European Organisation for Research and Treatment of Cancer Quality of Life Questionnaire C30 (EORTC QLQ-C30) version 3.0 will be applied [58]. The EORTC-QLQ-C30 is designed to be cancer specific, and consists of 30 items distributed throughout different functional and symptom scales [58]. To assess symptoms of depression and anxiety, the Hospital Anxiety and Depression Scale (HADS) version 3.0 will be used [59]. HADS comprises 14 items and is designed to measure general depression and anxiety by self-administration [59].

#### Physical activity

Level of physical activity will be measured by step counts using a Garmin Vivofit 3 activity tracker (Garmin, Olathe, Kansas, U.S.). The average number of steps walked measured over three consecutive days will be used as an estimate of physical activity.

#### Qualitative assessment of participants’ experiences

Qualitative semi-structured interviews will be conducted with a sample of participants from the intervention group post intervention to explore participants’ experiences and satisfaction with the intervention.

#### Treatment tolerance and toxicity

Data on dose-reductions and treatment discontinuations will be registered prospectively throughout the intervention period. Toxicity will be registered according to the NCI CTCAE v4.0.

#### Body measures

Weight, height and body mass index (BMI) will be assessed using standard procedures (no shoes, light clothing). Body composition will be assessed by whole-body dual-energy x-ray absorptiometry (DXA) scan (GE lunar iDXA, GE Healthcare Technologies, Madison, Wisconsin, U.S.), and by bioelectrical impedance (BI) assessment (Body Composition Monitor, Fresenius Medical Care, Bad Homburg v.d.H., Germany).

#### Inflammatory biomarkers

To explore the influence of exercise training on inflammation, data on inflammatory biomarkers C-reactive protein (CRP), interleukin 6 (IL-6), and Chitinase-3-like protein 1 (CHI3L1), also known as YKL-40, will be collected from medical records or through cooperative research projects.

#### Hospital admissions

Data on number, causes, and length of hospitalization during the study period will be collected from medical records.

#### Mortality/survival

Incidences of deaths and causes of deaths will be registered throughout the study period by review of medical records.

Frequency and timing of study assessments are shown in Table 2. REDCap will continuously be used for data entry during the study period, and subsequently for data storage.

**Table 2 Tab2:** Schedule of study assessments

Time (week no.)	-2 to 0	0	1	2	3	4	5	6	7	8	9	10	11	12	13	17
Enrollment																
Eligibility screen	X															
Informed consent	X															
Randomization		X														
Intervention			X---------------------------------------------------------------------------------------------------------------------------X													
Physical tests and examinations																
30s-CST (primary outcome)	X								X						X	X
6MWT	X								X						X	X
Handgrip strength	X								X						X	X
Gait speed test	X								X						X	X
Physical activity^a^	X														X	
DXA	X														X	
BI	X														X	
Body weight^a^	X								X						X	X
Inflammatory biomarkers	X								X						X	X
PROMs																
PRPS	X								X						X	X
MDASI^a^	X								X						X	X
EORTC-QLQ-C30	X								X						X	X
HADS	X								X						X	X
Qualitative exploration																
Individual Interviews															X	
Feasibility																
Adherence	X	X	X	X	X	X	X	X	X	X	X	X	X	X		
Attrition	X	X	X	X	X	X	X	X	X	X	X	X	X	X	X	X
Adverse events	X	X	X	X	X	X	X	X	X	X	X	X	X	X		
Oncological treatment																
Treatment related toxicity^b^	X	X	X	X	X	X	X	X	X	X	X	X	X	X	X	X
Dose-reductions^b^	X	X	X	X	X	X	X	X	X	X	X	X	X	X	X	X
Hospitalizations	X	X	X	X	X	X	X	X	X	X	X	X	X	X	X	X
Survival	X	X	X	X	X	X	X	X	X	X	X	X	X	X	X	X

^a^Once weekly for participants in the intervention group ^b^Registered for every treatment course

Abbreviations: *30s-CST* 30-s chair stand test, *6MWT* six-minute-walk-test, *BI* bioelectrical impedance, *DXA* whole-body dual-energy x-ray absorptiometry, *EORTC-QLQ-C30* European Organisation for Research and Treatment of Cancer Quality of Life Questionnaire C30, *HADS* Hospital Anxiety and Depression Scale, *MDASI* M.D. Anderson Symptom Inventory, *PRPS* patient-reported performance status

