### Statistics

#### Sample size

No prior studies have investigated the clinically important difference in the 30s-CST in patients with cancer. According to a previous study focusing on patients with osteoarthritis, the clinically important change in the 30s-CST was set at 2.6 repetitions [60]. Based on results from prior studies in patients with advanced cancer, a standard deviation (SD) of approximately 3 has been reported [61, 62]. To be able to detect a between-group difference in the within-group changes of 2.6 repetitions in the 30s-CST, and to obtain a type I error rate of 5% and a power of 90%, a sample size of 29 participants per study arm will be needed. To account for a dropout rate of approximately 40%, it has been decided to increase the group size to 50. Thus, a total of 100 participants will be included in the trial.

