#### Analyses

Feasibility measures will be reported as numbers and percentages. Baseline characteristics will be calculated for all participants (total), and separately for the intervention and control group. For all quantitative variables the median number and interquartile range (IQR) will be calculated, and for nominal variables the number and percentage distribution will be calculated. Results from physical tests, blood test, body measures, questionnaires, hospitalizations and toxicity-measures will be reported as means and SDs or as median and IQR, as appropriate. Change over time in ordinal categorical values will be evaluated by a trend test using logistic regression. Within-group and between-group differences in continuous-level data will be performed using independent T-tests. Overall and cancer specific survival will be analyzed with the Kaplan-Meier method, competing risk and Cox regression analyses. The significance level of all tests is set at *p* < 0.05 and analyses will be carried out in R by the program’s statistician (AT).

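### Survival is to be analysed with Kaplan-Meier, Cox and competing-risk methods, but the only schedule ends it at week 17 and the study period is undefined: state one common, later cut-off date

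*Protocol article*

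**What the plan says.** The Analyses section commits to formal survival methods: "Overall and cancer specific survival will be analyzed with the Kaplan-Meier method, competing risk and Cox regression analyses". The same paragraph sets the significance level of all tests at p < 0.05. Study outcome measures lists mortality among the secondary endpoints.

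On data collection, the Mortality/survival section says: "Incidences of deaths and causes of deaths will be registered throughout the study period by review of medical records". The article does not say whether the study period is each participant's time on study or the whole trial, and it gives no calendar date. Table 2, in the same section, marks survival in every column, and its last column is week 17. This agrees with the Abstract, which puts the last assessment after 16 weeks.

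The sample size rests on the chair stand test alone: "Thus, a total of 100 participants will be included in the trial". No event target, hazard ratio or expected survival time is given.

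**The concern.** Week 17 suits the chair stand test, which needs a visit. Vital status and cause of death come from medical records and need none. If survival is censored at week 17 for each participant, the trial drops deaths that the same record review could supply for everyone enrolled before the last participant. An analysis plan written later cannot recover deaths that were not collected, so the collection window matters more here than the choice of model.

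What is at stake is the precision of a secondary endpoint for which the article promises a hazard ratio and tests. The primary endpoint and the sample size are not affected.

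**Working it through.** **The plan's own figure.** The only sample-size figure concerns the chair stand test: a difference of 2.6 repetitions, SD 3, 5% type I error (taken as two-sided) and 90% power. The normal approximation gives 2 × 3² × (1.960 + 1.282)² / 2.6² = 28.0 per arm. The exact two-sample t-test gives 29 (power 0.900; 28 per arm gives 0.890). Allowing for 40% dropout, 29 / 0.6 = 48.3, so 49, stated as 50. The figures reproduce. For survival they supply only the ceiling of 100 possible deaths.

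**Inputs for survival.**
- From the article: 100 participants, 1:1 allocation, last scheduled survival entry at week 17 (about 3.9 months).
- Assumed, because the article gives neither: exponential survival with median m of 6, 9 or 12 months in both arms combined, and uniform accrual over A = 12 or 24 months. Vital status is taken as known for everyone.

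**Formulas**, with λ = ln 2 / m and t = 3.9 months:
- Deaths if everyone is censored at week 17: D = 100 × (1 − exp(−λt)).
- Deaths with a common cut-off at the last participant's week-17 date, so that follow-up runs from t to t + A: D = 100 × (1 − [exp(−λt) − exp(−λ(t + A))] / (λA)).
- 95% confidence interval factor for the hazard ratio: exp(1.96 × 2 / √D).
- Hazard ratio detectable with 80% power: exp(−(1.960 + 0.842) × 2 / √D).

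**Example, m = 6.** λ = 0.1155 and exp(−λt) = 0.637, so D = 36 at week 17. With A = 12, exp(−λ × 15.9) = 0.159 and λA = 1.386, so D = 100 × (1 − (0.637 − 0.159) / 1.386) = 66.

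| Assumed median (months) | Rule | Deaths | Ratio to week 17 | CI factor | HR for 80% power |
|---|---|---|---|---|---|
| 6 | week 17 | 36 | – | 1.9 | 0.39 |
| 6 | common date, A = 12 | 66 | 1.8 | 1.6 | 0.50 |
| 6 | common date, A = 24 | 78 | 2.2 | 1.6 | 0.53 |
| 9 | week 17 | 26 | – | 2.2 | 0.33 |
| 9 | common date, A = 12 | 52 | 2.0 | 1.7 | 0.46 |
| 9 | common date, A = 24 | 66 | 2.5 | 1.6 | 0.50 |
| 12 | week 17 | 20 | – | 2.4 | 0.29 |
| 12 | common date, A = 12 | 42 | 2.1 | 1.8 | 0.42 |
| 12 | common date, A = 24 | 57 | 2.8 | 1.7 | 0.48 |

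Ratios are taken before the deaths are rounded. Censoring at week 17 is 100 − 36 = 64% to 100 − 20 = 80%.

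**Limit of the gain.** For a hazard ratio of 0.70 with 80% power, the Schoenfeld formula needs 4 × (1.960 + 0.842)² / (ln 0.70)² = 247 deaths. The trial has 100 participants, so no length of follow-up reaches that.

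**The case against.** The strongest objection is that week-17 censoring is inferred. Table 2 schedules assessments per participant and does not state an administrative censoring date. The article speaks of the study period for deaths but of the intervention period for dose reductions, so the former may well mean the whole trial. The planned survival methods fit that reading too. This stands: a reader might conclude that the plan definitely stops at week 17, and the text does not support that. What remains is that Table 2 gives the only horizon, the text gives no later one, and the two need to be reconciled.

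It can also be said that an article may leave censoring rules to the full protocol or analysis plan. That is true of the details, but the article itself prints a collection window that ends at week 17 beside a promise of Cox and competing-risk analyses.

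Survival is secondary and has no event target to miss, so it cannot be called underpowered against the plan's own standard. Most of the added deaths would also fall after the 12-week intervention, so an effect confined to that period would be diluted. Both points stand. They limit the claim to a gain in precision, and they are the reason to keep week-17 mortality as a descriptive result.

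Three stronger readings fail:
- That nearly all times would be censored: the figure is 64% to 80% under these assumptions.
- That the gain is reliably two- to threefold: with 12-month accrual and a 6-month median it is 1.8.
- That few other-cause deaths would undermine the cancer-specific analysis: that analysis rests on cancer deaths, and few competing events means little distortion from them.

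**Conclusion.** The point holds as a cheap improvement and a needed clarification, not as an error that threatens the trial. If Table 2 governs, about 20 to 36 deaths would support the survival analyses, and 80% power would need a hazard ratio of about 0.29 to 0.39. A common cut-off date raises the deaths to about 42 to 78 and the detectable hazard ratio to about 0.42 to 0.53. These figures rest on assumed exponential medians of 6 to 12 months and accrual of 12 to 24 months. If the study period already means the whole trial, the loss does not arise and only the wording needs repair. A reader might infer that longer follow-up would make the survival comparison adequate. It would not for moderate effects, so the comparison is exploratory under either rule.

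**What to change.** - Define the study period for deaths and bring Table 2 into line with it. State one calendar date for administrative censoring, no earlier than the last participant's week-17 visit.
- Review medical records for vital status and cause of death for all randomised participants up to that date, including those who left the intervention or the physical tests, as far as consent allows.
- Stratify the Cox model by diagnosis (pancreatic, biliary tract, lung), because randomisation is stratified on it.
- Report mortality at week 17 by arm as a descriptive proportion.
- Label the survival comparison exploratory.

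The cost is one further record review, a few sentences, and confirmation that consent covers record access to the chosen date. The price in interpretation is possible dilution of an effect limited to the 12 intervention weeks. Sample size, visits and primary endpoint are unchanged.

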### Blinding procedures

Assessments of the primary outcome 30s-CST and all other physical tests will be performed by blinded physiotherapists. Due to the nature of the study, study participants are not blinded.

### Statistics

#### Sample size

No prior studies have investigated the clinically important difference in the 30s-CST in patients with cancer. According to a previous study focusing on patients with osteoarthritis, the clinically important change in the 30s-CST was set at 2.6 repetitions [60]. Based on results from prior studies in patients with advanced cancer, a standard deviation (SD) of approximately 3 has been reported [61, 62]. To be able to detect a between-group difference in the within-group changes of 2.6 repetitions in the 30s-CST, and to obtain a type I error rate of 5% and a power of 90%, a sample size of 29 participants per study arm will be needed. To account for a dropout rate of approximately 40%, it has been decided to increase the group size to 50. Thus, a total of 100 participants will be included in the trial.

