**Methods:**

PACE-Mobil-PBL is a two-armed randomized controlled trial. Participants will be randomized 1:1 to an intervention group (*N* = 50) or a control group (*N* = 50). Participants in the intervention group will receive standard oncological treatment and a 12-week multimodal intervention, comprised of: (I) supervised exercise training, twice weekly in the hospital setting, (II) home-based walking with step counts and goal-setting, (III) supportive and motivational nurse-led counseling, and (IV) protein supplement after each supervised training session. Participants in the control group will receive standard oncological treatment. The primary outcome is physical function measured by the 30-s chair stand test. Secondary outcomes include measures of feasibility, activity level, physical capacity and strength, symptom burden, quality of life, toxicity to treatment, dose reductions, inflammatory biomarkers, body weight and composition, hospitalizations and survival. Assessments will be conducted at baseline, and after 6, 12 and 16 weeks.

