### Study outcome measures

The primary endpoint is the between-group difference in within-group changes in physical capacity and lower extremity strength measured with the 30-s chair stand test (30s-CST) at the post-intervention assessment. Secondary endpoints include feasibility measures, adverse events, and changes in functional performance, muscle strength, body composition, body weight, patient-reported performance status, symptom burden, symptoms of depression and anxiety, QoL, physical activity, treatment tolerance and toxicity, inflammatory biomarkers, hospital admissions and mortality. The outcome measures for both groups are described in the following section.

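### The t-test named for the primary endpoint leaves out everyone without a post-intervention value, with about 40% dropout expected; a repeated-measures model should replace it

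*Protocol article*

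**What the plan says.** Study outcome measures defines the endpoint: "The primary endpoint is the between-group difference in within-group changes in physical capacity and lower extremity strength measured with the 30-s chair stand test", taken at the post-intervention assessment. Analyses names the test: "Within-group and between-group differences in continuous-level data will be performed using independent T-tests". No other method is named for a continuous outcome.

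Sample size assumes a difference of 2.6 repetitions, an SD of about 3, 5% type I error and 90% power, and concludes that "a sample size of 29 participants per study arm will be needed". The step to the enrolled number is "To account for a dropout rate of approximately 40%, it has been decided to increase the group size to 50".

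The 30s-CST is measured more often than the test needs. The abstract states: "Assessments will be conducted at baseline, and after 6, 12 and 16 weeks". Table 2 places these visits in the columns for weeks 7, 13 and 17. Apart from the enlarged sample, attrition appears only as a number and percentage under Feasibility measures.

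**The concern.** A t-test on change needs a baseline and a post-intervention value. With 40% dropout, about 20 of the 50 participants in each arm would have no place in the primary comparison, although many may have a week-7 result.

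In this population, leaving is unlikely to be unrelated to the outcome. The Background links cachexia and sarcopenia to impaired function and higher mortality, and the Discussion expects a high incidence of both. The arms also differ in what they ask of participants: one attends hospital training twice a week, the other does not, and neither is blinded. If weaker participants leave one arm more selectively than the other, the remaining groups are no longer comparable as randomised. The error can go either way. Selective loss from the training arm can suggest a benefit that is not there. If decliners leave both arms under one rule while the intervention works, more controls are lost and the effect is diluted.

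**Working it through.** **1. The plan's own figures.** Inputs from Sample size: difference 2.6, SD 3, alpha 5% (taken as two-sided), power 90%.

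- Normal approximation: n = 2 × (1.960 + 1.282)² × 3² / 2.6² = 27.98 per arm. The t-based solution is 28.97, so 29, with power 90.0%. The plan's figure reproduces.
- Dropout: 29 / (1 − 0.40) = 48.3, so 49; the plan takes 50. Expected evaluable: 50 × 0.60 = 30 per arm, power 91.0%.

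The arithmetic is sound. It concerns numbers only and says nothing about who is lost.

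**2. No true effect: bias and type I error.** Assumptions not in the article: SD of change 3 at weeks 7 and 13; correlation 0.6 between the two changes; logistic dropout with log-odds 1 or 1.5 per SD of worse change; every participant has a week-7 value. There are 50 per arm and 8,000 simulated trials per row. The likelihood analysis uses the week-7 change of everyone and the week-13 change where observed.

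| Dropout (intervention / control) | t-test bias | t-test error | Likelihood bias | Likelihood error |
|---|---|---|---|---|
| 40/40, random | 0.00 | 5.5% | 0.00 | 5.0% |
| 40/40, same week-7 rule | 0.00 | 5.0% | 0.01 | 5.0% |
| 40/40, same week-13 rule | −0.01 | 5.2% | −0.01 | 5.1% |
| 50/30, week-7 driven | 0.27 | 6.2% | −0.02 | 4.7% |
| 50/30, week-13 driven | 0.50 | 10.7% | 0.35 | 7.7% |
| 40/40, week-7 driven in intervention arm only, log-odds 1 | 0.60 | 11.9% | −0.01 | 5.0% |
| same, log-odds 1.5 | 0.77 | 16.7% | 0.00 | 4.8% |
| 40/40, week-13 driven in intervention arm only, log-odds 1 | 1.00 | 25.9% | 0.66 | 15.7% |
| same, log-odds 1.5 | 1.28 | 40.9% | 0.86 | 23.3% |

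Bias is in repetitions. In the week-13 rows, dropout depends on a value that is never seen.

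**3. A second set of assumptions.** Visit SD 3, correlations between visits 0.65 to 0.75, log-odds 0.6 to 1.0 per repetition of week-7 change, dropout 40% in both arms.

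- Informative in the intervention arm only: bias +0.6 to +0.8 repetitions, type I error 16 to 26%.
- Control slope half the intervention slope: bias about 0.24, type I error 6.3 to 6.4%.
- Same slope in both arms: 5.1 to 5.2%.

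The one-arm error rates exceed those in step 2 partly because the SD of change is smaller. With a correlation of 0.65 it is 3 × √(2 × (1 − 0.65)) = 2.5. The dropout link is also steeper: at a correlation of 0.75 the week-7 change has SD 3 × √(2 × 0.25) = 2.12, so the slopes equal 1.3 to 2.1 per SD.

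**4. True effect of 2.6, one outcome-dependent dropout rule in both arms** (assumptions of step 2, 40% overall). The t-test estimate falls to 2.34 and 2.20 (week-7 driven) or 2.18 and 1.94 (week-13 driven). Power falls to between 79% and 85%. Dropout is then about 29 to 32% in the intervention arm and 49 to 51% in the control arm.

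**5. Precision when dropout is random.** With 60% observed and correlation 0.6, the variance ratio of likelihood to t-test is 1 − 0.6² × 0.4 = 0.856. Its square root is 0.925, an SE about 7% smaller. Simulated power rises from 90.4% to 94.4%. Under the assumptions of step 3, with baseline also used, the SE is about 13% smaller.

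**The case against.** **The article never says that only completers are analysed.** True. A reader might infer a declared completers-only analysis, but the article defines no analysis set and no handling of missing values, and a t-test can follow imputation. Those details commonly sit in an analysis plan, which is not shown, so their absence is no fault here. What stands is narrower: the article names the test and sizes the trial on the evaluable remainder, and that test by itself has no way to use the interim measurement.

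**The large error rates come from an extreme scenario.** Also true. A reader might infer that 40% dropout will inflate the type I error. With no true effect and the same mechanism in both arms, it does not. Figures of 12% or more need strongly informative dropout in one arm and random dropout in the other. No figure in the article supports that, and disease-related decline will drive loss in both arms to some degree.

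**The proposed model is shown at its best.** This stands in part. Near-zero bias requires that dropout depends on observed values and that leavers have a week-7 result. When half the dropout was placed before week 7, under the one-arm mechanism, a likelihood estimate kept a bias of +0.23 to +0.31, against +0.58 to +0.68 for the t-test. With week-13-driven differential dropout, its type I error was 7.7 to 23.3%. It was still the better of the two in each of these cases.

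**Conclusion.** The concern holds as a should-fix point. The sample size calculation is correct. The weakness is the pairing of the named primary test with an expected loss of about 40%, when a mid-intervention 30s-CST is already scheduled.

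The size depends on assumptions that the article does not supply:

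- same dropout mechanism in both arms, no effect: about 5% type I error;
- moderate differences between arms: about 6 to 11%, bias about 0.2 to 0.5 repetitions;
- week-7-driven dropout in one arm only: about 12 to 26%, bias about 0.6 to 0.8 repetitions;
- real effect of 2.6 with a shared outcome-dependent rule: estimate diluted to about 1.9 to 2.3 repetitions.

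The documents do not support saying that the primary result will be biased or that the trial is invalid. They support saying that the stated test is exposed to a plausible bias that enlarging the sample cannot remove, and that a better method is available with data already planned.

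**What to change.** In Analyses, replace the t-test for the primary endpoint with a linear mixed model for repeated measures, or a constrained longitudinal model. Include all randomised participants in their allocated arm. Use the 30s-CST at baseline and at the 6-, 12- and 16-week assessments, arm-by-visit terms and diagnosis, which is the stratification factor. The 12-week contrast between arms is the primary estimate. Keep the t-test on observed change as supportive.

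Because the model relies on data missing at random and cannot recover the outcomes of those lost before the interim visit, add a sensitivity analysis for data not missing at random and for deaths. Its details can go in the analysis plan.

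The cost is additional analysis work and a change to the published primary method, which should be made before unblinded outcome data are examined. No new visits and no larger sample are needed. If dropout is in fact harmless, the change still gains precision, with an SE about 7 to 13% smaller under the assumptions above.
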